**Fig. 1 Fig1:**
[figure not shown]
Consolidated Standards of Reporting Trials (CONSORT)-style flow diagram

Two questions will be used for initial screening:Can the patient follow a two-stage command, judged clinically?Was the patient walking without help from another person before this stroke?

All subjects who answer “yes” to both questions are eligible and will be entered into the consent and selection process. An investigator will explain the consent form, and allow the person ample time to read through the consent form and ask questions. If they agree, they will acknowledge consent by signing the form. All potential participants will have up to 24 hours to decide whether they want to partake in this study. All actual participants will have given informed consent, signed by them or by an independent witness if necessary, before they are registered.

Patients will be eligible if they:Are aged 40–75 yearsHad onset of stroke less than 4 months agoAre being admitted for rehabilitation for the first timeWere able to walk at least 10 m prior to stroke, without help of another person; use of equipment allowedHave sufficient cognition to participate in the study and testing procedures (clinically judged, because there are no valid short cognitive measures to assess ability to consent and participate)Can follow a 2-stage command (e.g. pick up an object, put it on the table)Have sufficient visual function to see the watch feedback (clinically judged)Have the capacity to consent and then give consent to participate in the study

Entry may be delayed after admission if a person satisfied all other criteria but was not yet able to follow a 2-stage command. In this case, 3-day follow up will be performed, and the patient will be eligible if they then meet that criterion. This was added to allow for patients transferred within 1 or 2 weeks of a stroke, and patients who become confused by the move from another hospital. Patients admitted a second time within the study period will be excluded.

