Participants will be randomly assigned to one of two groups: (1) feedback of activity levels; or (2) no feedback of activity levels (i.e. control group). A block stratified randomization approach with two strata will be used, based on walking speed at the time of recruitment. A threshold of 0.42 m/s [12] will be used to define two groups: slow walkers (< 0.42 m/s) unlikely to walk in the community, and moderate-fast walkers (> 0.42 m/s). People unable to walk at the time of recruitment will be classified as slow walkers. The block size will be 5.

Once recruited, the recruiting doctor will inform the research office personnel, who are not blinded, and they will then undertake allocation. Allocation will be performed using a computer program in Microsoft Excel to allocate groups and generate numbers for each stratum (slow walkers or not slow walkers); the allocation will be made by the research office staff after registration. The research office will then notify the ward about the patient’s allocation by telephone. The researchers who will be performing all assessments will remain blinded to group assignment throughout the study.

The participants’ rehabilitation programmes will continue as normal, with no change in relation to this study. Therapists will not specifically be informed about a participant’s group, but may learn this. However therapists will not specifically encourage use of the feedback (or the opposite).

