#### Data collected

The assessment schedule is shown in Fig. 4. The researchers will collect the following demographic and medical information from clinical notes on admission to rehabilitation: age, sex, height, weight and dates of stroke onset and admission. Moreover at each contact the research doctors will ask the patient about any problems with the watch, and will look out for any observable adverse effects such as a skin rash. The primary data will be the daily activity counts generated by the Smart watch and downloaded daily by the researcher.

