#### Data handling and analysis

The data will be collected by researchers on the ward using prepared forms. The forms will be given to the research office where they will be entered into an Excel spreadsheet database. The paper forms will be stored in secure, locked files. De-identified and encrypted data will then be sent electronically on a weekly basis to Oxford Brookes University where they will be checked (a) for obvious errors (e.g. data outside the possible range) and (b) for missing data. If needed, the research centre in Hefei will be contacted to clarify apparent errors and to confirm whether missing data are truly absent. The electronic data will be stored in a secure database at Oxford Brookes University, but all investigators will have free access to all electronic data.

The following measures will be compared between the two intervention groups: Barthel ADL index, Rivermead Mobility Index, Fatigue Severity Scale, Montreal Cognitive Assessment, WHO Disability Assessment Scale, EuroQol 5D-5L, and length of inpatient stay. Data will be analysed based on the intention-to-treat principle.

Descriptive statistics will be calculated for demographic characteristics and compliance data. The independent samples or the chi-square (X^2^) test will be used to assess differences between group means and frequencies at baseline, the test being chosen according to data type. Measures that differ significantly between the two groups will be included as covariates in statistical models comparing interventions. The distribution of data will be analysed.

SPSS v23 will be used to investigate progression within groups by regression analysis. The frequency that each person achieves their activity goal, as set automatically by the watch, will be explored within the intervention groups at discharge from inpatient rehabilitation.

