For outcome data, the linear mixed models (LMM) procedure in SAS 9.4 will be used to determine the mean changes in measures, as response variables, according to two intervention regimes (intervention and control) and three repeated measurements, using baseline as a covariate. Distribution of the data will be checked according to various methods of analysis, which are employed at different stages of the study. The analysis of outcome, which will be based on LMM, assumes a Gaussian distribution that can be checked and tested by standard methods. However, we also note that LMM is, in general, quite robust to violation of the distributional assumptions.

This model treats all factors as categorical, and so different types of data can be used. Further and based on the differences in least squares (marginal) means between the two groups (intervention vs control), provided by LMM analysis, power, effect size (Cohen’s d) and their 95% non-central confidence limits will be calculated. Analysis will be used for each outcome measure. The “group” term is the intervention group; the “time” term is the assessment time point. The group-by-time interaction effect will reveal if there is a greater change over time in one group compared with the other.

For a sample size estimate, we used a conservative estimate of the standardised effect size of change in physical activity levels from the initial assessment to discharge from inpatient rehabilitation (i.e. the first phase of the study) as our primary outcome of interest. Our pilot work suggests an effect size of 0.12, and for alpha 0.05 and power 0.95 for repeated measures with three measurement points, we expect a sample of 182 to be adequately powered. From pilot work we expect 10% to drop out, and so we propose to recruit 200 patients.

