## Discussion

This study investigates whether setting personalized activity goals derived from and coupled with personal and early feedback on the amount of activity undertaken throughout each day can enhance self-generated activity levels, and whether any increase is associated with improved functional outcomes. The study design integrates the novel intervention into current practice which ensures that the results should be generally applicable. This discussion will cover acknowledged weaknesses and limitations, some arising from technological and financial limitations and others, which follow on from new information published after the protocol was finalized in July 2015. The discussion will also cover strengths and potential outputs in terms of new knowledge.

Technological and financial limitations underlie many of the weaknesses. The watch is only worn during the five working days and only for nine working hours each day. Ideally the watch would record activity and provide feedback throughout the whole time a patient is awake, including weekends and evenings. This limitation reflects constraints associated both with the watch and with the setting. Data storage is limited, which means that only 20% of the activity can be recorded. In addition, download of data is required each day, which requires a trained person, who is only available in working hours. Third, the watch needs charging each day, again requiring a trained person. With advances in technology these constraints should be overcome.

The goal-setting algorithm designed to make allowance for natural daily routines such as time of getting up, meal times etc. is rigid, with fixed 2-hour slots. The increment chosen - 5% - was arbitrary and further studies may be needed to discover whether there is any better increment. The increment may need to vary over the course of recovery. In the early days and weeks quite large increases will occur naturally, but over time the natural rate of change drops and a stable increment might be more applicable after the first 3 months. The visual feedback display seems appropriate, but again there may be better designs; there is always a compromise between detail and simplicity. Recent research suggests that feedback coupled with goal setting can be effective [11], and so an improvement in technology coupled with increasing knowledge may make the goal setting and feedback system more effective.

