A third limiting factor arises from the funding and timing of inpatient rehabilitation in Hefei, which starts quite late after stroke and is limited to 2 or 3 weeks of inpatient rehabilitation, limiting the time the intervention can be applied. By the time a person is admitted, they have already established a pattern of behaviour. Also, it may take at least 1 week to become familiar with the device and its purpose and, because changing behaviour takes time, the intervention may be too short to lead to any detectable difference between the groups. It was not possible to provide the watch for use at home, mainly for practical reasons (daily data downloads and recharging). Ideally the intervention should be continued over many weeks.

The research funding was limited. The research data were collected by the ward doctors, who were specifically trained and collected the clinical data as part of their normal work. However, this limited the options of using more fixed procedures, for example when checking cognitive ability. This will not cause any bias, but may slightly limit generalizability.

Last, it has been assumed that increasing general, non-specific activity levels will lead to specific changes in mobility and independence is activities. This assumption is reasonable, but the strength of the relationship is unknown and a much larger study may be needed to show any actual benefit.

One strength is that, according to our calculations, the study is adequately powered; we will recruit about 200 patients. Second, the study is embedded with daily clinical routines in a busy hospital, such that if the intervention is effective, it should be easy to continue the intervention.

If this study does not show an effect, there will still be worthwhile knowledge generated. The study will give an estimate of variance in the measures used, which will help in future power calculations. It will discover whether a short episode of feedback on activity set against goals might have an effect. Failure to find an effect should not be taken as proving the intervention is ineffective, given the limitations identified. The study will give information about the feasibility of collecting data in a trial set within a standard rehabilitation programme in China (Additional file 1).

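### Time since stroke, which the protocol itself links to natural gain, can enter the analysis only through a baseline significance test; this costs some precision but does not bias the comparison

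*Protocol article*

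**What the plan says.** - **Natural change.** The Discussion, when considering the 5% goal increment, says: "In the early days and weeks quite large increases will occur naturally, but over time the natural rate of change drops".
- **Who enters.** The eligibility list under Methods, Design, requires onset under 4 months ago and sets no lower limit. The delayed-entry provision was added "to allow for patients transferred within 1 or 2 weeks of a stroke". The limitations in the Discussion describe inpatient rehabilitation in Hefei as a service "which starts quite late after stroke and is limited to 2 or 3 weeks of inpatient rehabilitation".
- **Randomisation.** "A block stratified randomization approach with two strata will be used, based on walking speed at the time of recruitment". The threshold is 0.42 m/s, and time since stroke plays no part.
- **Data.** The section Data collected lists "age, sex, height, weight and dates of stroke onset and admission", so time since stroke can be derived for everyone.
- **Model.** Data handling and analysis describes a linear mixed model with group, time and their interaction over "three repeated measurements, using baseline as a covariate".
- **Other covariates.** The same section gives one rule: "Measures that differ significantly between the two groups will be included as covariates in statistical models comparing interventions".

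**The concern.** The powered outcome is the change in activity score between the first assessment and discharge, a period of at most 3 weeks. By the protocol's own account, the natural part of that change depends on how long ago the stroke was. Two patients with the same first-day score, one a few weeks and the other over three months after onset, would be expected to gain differently. A baseline level does not carry that information, and neither does a walking-speed stratum except indirectly.

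Two things are at stake. Differences in recovery rate between patients stay in the error term, which widens the confidence interval. And if the arms happen to differ in time since stroke, but not significantly, the estimate moves with that difference and nothing in the stated analysis corrects it.

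**Working it through.** **1. The plan's own sample size.** Stated inputs: effect size 0.12, alpha 0.05, power 0.95, three measurement points, 182 evaluable patients. Read 0.12 as Cohen's f for the group-by-time interaction, and assume a correlation between measurements of rho = 0.5 and sphericity (neither is stated). The noncentrality is

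lambda = f² × N × m / (1 − rho) = 0.12² × 182 × 3 / 0.5 = 15.7,

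with 2 and 360 degrees of freedom. Power is 0.952, and 182 is the smallest even N that reaches 0.95. The figure reproduces. With rho = 0.3 or 0.7 the answer would be 252 or 110. Read instead as a standardised difference between two means, 0.12 would need 3,610 patients and 0.24 would need 904, so neither is the effect that 182 was planned for.

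**2. The planned effect in SDs of change.** At rho = 0.5 the SD of change is sqrt(2 × (1 − 0.5)) = 1 SD of a single measurement.

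- Arms diverging linearly: cell effects are ±a at the first and last points, so f = a × sqrt(2/3), a = 0.12 / 0.816 = 0.147, and the difference in change is 4a = 0.59 SD. Check: 0.588² × 91 / 2 = 15.7 = lambda.
- Effect present by the second point and then held: f = D / sqrt(18), so D = 0.12 × 4.243 = 0.51 SD.

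**3. Chance imbalance.** Trial status reports 160 recruited, or about 80 per arm. The SD of the standardised imbalance in any baseline variable is sqrt(2/80) = 0.158. The two-sided 5% limit is 1.96 × 0.158 = 0.310 SD.

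**4. Shift in the estimate.** Let r be the correlation of time since stroke with activity change, after what the model already holds. The documents do not give r, so a range is assumed. Shift at the limit = r × 0.310; fall in residual variance = r².

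| Assumed r | Shift (SD of change) | Share of 0.59 | Share of 0.51 | Fall in residual variance |
|---|---|---|---|---|
| 0.2 | 0.062 | 11% | 12% | 4% |
| 0.3 | 0.093 | 16% | 18% | 9% |
| 0.4 | 0.124 | 21% | 24% | 16% |

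These shifts are at the edge of non-significance. A one-SD imbalance (0.158) shifts the estimate by about half as much, 0.03 to 0.06 SD.

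**5. Power of the reproduced interaction test**, with lambda divided by (1 − r²):

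| N | Unadjusted | r = 0.2 | r = 0.3 | r = 0.4 |
|---|---|---|---|---|
| 182 | 0.952 | 0.959 | 0.968 | 0.978 |
| 160 | 0.922 | 0.933 | 0.945 | 0.960 |
| 144 (160 less 10%) | 0.891 | 0.904 | 0.919 | 0.939 |

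**6. The baseline-test rule.** For each setting, 20,000 two-arm trials of 182 patients were simulated and analysed three ways.

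- The rule is triggered in about 5% of trials (4.6% to 5.2%).
- With no effect, unadjusted type I error is 0.048 to 0.050 for r = 0.2 to 0.5. Always adjusting gives 0.051. The rule gives 0.048 at r = 0.2 and 0.043 at r = 0.5.
- With an illustrative difference of 0.24 SD, power is as follows. (This is smaller than the planned effect in step 2; only the contrast between methods matters.)

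| r | Unadjusted | Rule | Always adjusted |
|---|---|---|---|
| 0.2 | 0.363 | 0.363 | 0.376 |
| 0.3 | 0.358 | 0.357 | 0.387 |
| 0.5 | 0.365 | 0.363 | 0.456 |

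- Among trials with a baseline imbalance of |t| > 1.5 and no effect, unadjusted type I error is 0.061, 0.088 and 0.119 at r = 0.2, 0.3 and 0.5. Adjusted, it is 0.052 to 0.054.

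**The case against.** - **Randomisation already deals with this.** Allocation is random and described as concealed, so time since stroke balances on average and the standard error already allows for chance imbalance. This stands. A reader might infer that unequal natural recovery can mask or mimic a feedback effect in a systematic way. The documents do not support that: the simulated type I error of the unadjusted analysis is about 5%. The inflation in step 6 arises only after conditioning on an unlucky allocation.
- **The plan does have a covariate rule.** This also stands. It would be wrong to say that the analysis ignores time since stroke altogether, because a significant imbalance could bring it in. But the rule acts only on the rare large imbalance, leaves all smaller ones alone, and recovers almost no precision.
- **The spread may be narrow.** The sentence on natural change concerns the goal increment and gives no rate, so it cannot be read as saying that the decline is steep. The mention of 1 or 2 weeks explains a delayed-entry provision, while the limitations say rehabilitation starts late. Very early patients may be few, which would lower r. Baseline activity and walking speed may also absorb part of the variation. All of this is fair and is why r is shown as a range; none of it closes the window set by the eligibility list.
- **An article may leave covariates to the analysis plan.** That would answer the point if the article were silent, but it states a specific rule for choosing covariates. That rule is what is questioned here.

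**Conclusion.** The point holds as a matter of precision, not of validity. A recorded variable that the protocol itself ties to natural gain has no fixed place in the stratification or the model, and the only stated route into the analysis is a significance test that rarely fires and gains almost nothing.

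The size is modest. An imbalance at the significance limit, with 80 per arm, moves the difference by 0.06 to 0.12 SD of change, or about 11% to 24% of the planned effect. Comparing that shift directly with the stated 0.12 makes the two look equal, but the scales differ: as Cohen's f for the interaction, 0.12 corresponds to about 0.51 to 0.59 SD of change.

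These figures rest on an assumed r of 0.2 to 0.4, on rho = 0.5 with sphericity, and on reading 0.12 as Cohen's f. The stated sample size is unaffected. The gain is still worth having, because recruitment ended at 160, below the 182 evaluable patients the plan called for.

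**What to change.** Prespecify time from stroke onset to randomisation as a covariate in the activity model and in the clinical-scale models, whatever its baseline balance. Log days is a reasonable form, with a term by time point so that it acts on the change and not only on the level. For this variable, the fixed covariate replaces the baseline-significance rule.

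The cost is a change of analysis wording and one or two degrees of freedom. No new data are needed, since the onset date is already collected. A table of activity change by arm for earlier and later patients, for example split at the median, is an optional descriptive display.

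Recruitment and follow-up have ended. If outcomes by arm have already been seen, the adjusted analysis should be reported alongside the stated one and labelled as added later.

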## Trial status

At the time of original submission (20 February 2017) recruitment in the trial had started and 88 patients had been recruited. Recruitment ended with 160 patients on 16 June 2017 with final follow up on 16 September 2017.

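### The Discussion rests adequate power on about 200 recruits, but recruitment closed at 160, below the 182 needed even before dropout; the stated 0.95 power should be restated.

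*Protocol article*

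**What the plan says.** The sample size paragraph, at the end of Data handling and analysis in the protocol article, gives these inputs: "Our pilot work suggests an effect size of 0.12", and "for alpha 0.05 and power 0.95 for repeated measures with three measurement points". From them it derives 182 patients. It then adds an allowance for loss: "From pilot work we expect 10% to drop out, and so we propose to recruit 200 patients". The opening of Methods repeats the target of 200 and reports 88 recruited at the time of original submission.

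The Discussion names sample size as the first strength of the study: "the study is adequately powered; we will recruit about 200 patients".

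Trial status, the last section, reports the outcome: "Recruitment ended with 160 patients on 16 June 2017". The article gives no reason for closing below target and no revised power, and the Discussion is not corrected.

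**The concern.** The adequate-power statement has a single stated basis, a sample of about 200, and the same article reports that this sample was not reached. The 160 recruited falls short of the analysed number, not only of the inflated recruitment target, so the gap does not depend on how many patients drop out.

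What is at stake is how a null result is read. The Discussion itself warns that the intervention may be too short to produce a detectable difference, so a null result is a realistic possibility. It also cautions that such a result would not prove the intervention ineffective, but it ties that caution to the limitations it has listed. Sample size is not among them; it is listed as a strength. A reader would therefore weigh a null result against a power that the trial does not have.

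**Working it through.** **Inputs from the protocol article.** Effect size 0.12, alpha 0.05, target power 0.95 and three measurement points (Data handling and analysis); two groups ("Participants will be randomly assigned to one of two groups"). The effect tested is taken as the group-by-time interaction, because the analysis text says: "The group-by-time interaction effect will reveal if there is a greater change over time in one group compared with the other".

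**Assumptions, not stated in the article.** The 0.12 is Cohen's f; allocation is equal; the correlation between repeated measurements (rho) is 0.5; sphericity holds (epsilon = 1).

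**Formula.** Noncentral F test for the interaction, with k = 2 groups and m = 3 points:
- noncentrality = f² × N × m / (1 − rho)
- df1 = (k − 1)(m − 1) = 2
- df2 = (N − k)(m − 1)

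**Reproducing the plan's figure.** For N = 182, noncentrality = 0.0144 × 182 × 3 / 0.5 = 15.72 and df2 = 360. Power is 0.952, and 182 is the smallest even N that reaches 0.95. Other readings do not return 182: 0.12 as Cohen's d for two means needs 3610 in total (two-sided), and a between-groups F test needs 604.

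**Dropout allowance.** 182 / 0.9 = 202.2, so 203; 182 × 1.1 = 200.2, so 201. The stated 200 is close to both.

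**What was recruited.**
- Against the target: 200 − 160 = 40 short.
- Against the analysed number, with no loss: 182 − 160 = 22 short.
- With the plan's 10% loss: 160 × 0.9 = 144, and 182 − 144 = 38 short.

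**Power on the same inputs.**

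| N contributing | Noncentrality | df2 | Power | Type II error | Relative to 0.05 |
|---|---|---|---|---|---|
| 182 | 15.72 | 360 | 0.952 | 0.048 | about 1.0 |
| 160 | 13.82 | 316 | 0.922 | 0.078 | about 1.6 |
| 144 | 12.44 | 284 | 0.89 | 0.11 | about 2.2 |

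The effect detectable with power 0.95 rises from f = 0.12 to about 0.127 at 160 and 0.134 at 144.

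**Sensitivity to the unstated assumptions.**

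| Assumption | N needed for 0.95 | Power at 160 | Power at 144 |
|---|---|---|---|
| rho 0.4, epsilon 1 | 216 | 0.87 | 0.83 |
| rho 0.5, epsilon 1 | 182 | 0.92 | 0.89 |
| rho 0.6, epsilon 1 | 146 | 0.97 | 0.95 |
| rho 0.5, epsilon 0.75 | 224 | 0.86 | 0.82 |

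Of these settings, only rho 0.5 with sphericity returns the stated 182. If rho is instead tuned so that 182 gives exactly 0.95 (rho about 0.495), power is 0.920 at 160 and 0.888 at 144, so the result does not depend on rounding.

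**The case against.** The best defence is that the shortfall is disclosed. Trial status gives the 160 openly, and the Discussion sentence is written in the future tense, which fits the original submission, when 88 had been recruited. It is probably text that was not updated. That stands as an explanation, but the published article still carries both statements and does not reconcile them.

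A second defence is that the Discussion claims adequate power, not 0.95, and that many would call 0.89 to 0.92 adequate. This stands in part. A reader might infer that the trial is badly underpowered; on the inputs that reproduce 182, it is not. What fails is the design target of 0.95 and the premise of 200 patients on which adequacy was argued.

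Third, a reader might infer flatly that type II error has more than doubled. That holds only if 144 contribute. With all 160 it is about 1.6 times. The plan specifies intention-to-treat analysis with linear mixed models, which can use partial data from people who leave early, so the effective information may lie between the two cases.

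Fourth, it is tempting to treat rho 0.5 and sphericity as the plan's own. The article states neither, and it does not say that 0.12 is Cohen's f. They are back-calculated from 182 and must be labelled as assumptions.

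Finally, because the sample size text speaks of change from initial assessment to discharge, a reader might infer that power is lower still for a two-point comparison. That is a question about the model and not about recruitment: under such a model the planned 182 would already miss 0.95. Nor does the article show that the same effect size and correlation would carry over.

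**Conclusion.** The point holds. On the article's own figures, 160 recruited cannot supply the 182 analysed patients required, whatever the dropout, and the Discussion's strength claim conflicts with Trial status. The sample size arithmetic itself is sound; the fault is a claim left unreconciled with the recruitment outcome.

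The shortfall is about 3 points of power if all 160 contribute and about 6 points if 144 do. Those sizes rest on f = 0.12, equal groups, rho 0.5 and sphericity. The lower correlation and the departure from sphericity shown above make power worse; a correlation of 0.6 would bring it back to about 0.95 even at 144, but that setting would have required only 146 patients and so does not match the stated 182. The consequence is confined to how the result is interpreted, since recruitment and follow-up had ended.

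**What to change.** In the Discussion, replace the claim based on about 200 patients with the achieved numbers: 160 recruited against a target of 200, with about 144 to 160 expected to be analysable against the 182 required. Give the reason why recruitment closed early, if known.

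Restate power as about 0.89 to 0.92 for an effect size of 0.12 at three measurement points. Name Cohen's f, correlation 0.5 and sphericity as assumptions, and give the range at 144 (about 0.83 at correlation 0.4 to 0.95 at 0.6).

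Move sample size from the strengths to the limitations, so that the existing caution about a null result covers it.

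The cost is wording only. No design, data or analysis change follows; the stated power becomes somewhat less favourable.
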